## Abstract

**Background:**

For patients with treatment-naïve carcinoma of the prostate, hypofractionated irradiation becomes more and more popular. Due to the low α/β value of prostate cancer, increased single dose leading to a shortened treatment period seems to be safe and feasible. However, reliable data is lacking for post-prostatectomy patients so far. Further, the role of proton therapy is still under debate. Two prospective phase II trials with both, hypofractionated photon and proton therapy, provided promising results.

**Methods/ design:**

The PAROS trial is a prospective, multicenter and randomized phase III trial for men with localized prostate carcinoma after surgery. Post-prostatectomy patients will be randomized to either normofractionated radiotherapy (nRT) with photons (70.0/ 2.0 Gy), or hypofractionated radiotherapy (hRT) with photons (57.0/ 3.0 Gy) or hRT with protons (57.0/ 3.0 Gy relative biological effectiveness [RBE]). Block randomization is stratified by Gleason Score (≤ 7 vs. > 7) and treatment indication (adjuvant vs. salvage). The trial is planned to enroll 897 patients. The primary objective is to show an improvement in the bowel-score according to EORTC QLQ-PR25 after proton therapy compared to photon irradiation (week 12 vs. baseline). Secondary aims are non-inferiority of hRT compared to nRT with regard to biochemical progression-free survival (bPFS), overall survival (OS), quality of life and toxicity.

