## Methods

### Primary and secondary endpoints

The primary endpoint is defined as the change in the bowel-score according to EORTC QLQ-PR25 from baseline to 12 weeks after start of proton therapy compared to photon irradiation.

Secondary endpoints are bPFS after 5 years, quality of life (QoL) according to EORTC QLQ-C30 and –PR25 after 2 and 5 years, clinical symptoms and toxicity according to National Cancer Institute Common Terminology Criteria for Adverse Effects (NCI CTCAE) version 5.0 after 2 and 5 years as well as overall survival (OS) after 5 years.

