### Sample size calculation

The sample size calculation is based on the primary endpoint change in the bowel-score according to EORTC QLQ-PR25 from baseline to 12 weeks. Based on numerous trials, we assume a change of 6.5 points in the standard arm (arm 1). Based on the two phase II trials mentioned above, we assume a change of 6.5 points in arm 2 as well and a change of 2.5 points in arm 3. Equal standard deviation of 15 points is expected for all arms. In the primary analysis, arm 1 will be compared with arm 3 and arm 2 with arm 3. To control the overall type I error of 5%, local significance levels of 2.5% according to Bonferroni were applied in the sample size calculation. To achieve a power of 80% with the assumptions above, a sample size of 269 per arm results for the two-sided t-test. Calculations have been performed using PASS 14.0.8. The primary analysis will be performed applying the Bonferroni Holm procedure and the factors used in the stratified randomization will be considered. This will lead to an increase in power. Based on the experiences from previous studies, a conservative rate of drop-outs and loss to follow-ups of 10% is expected. To compensate for this loss in information, 299 patients per arm are required resulting in a total of 897 patients to be randomized.

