### Statistical analysis

In the primary analysis, arm 1 vs. arm 3 and arm 2 vs. arm 3 will be compared regarding the primary endpoint applying a linear regression model including the stratification variables used in the randomisation procedure and center. Primarily, the analysis will be based on the Intention to treat population which consists of all randomized patients treated at least for 1 week in the arm as randomized. Missing values for the primary endpoint will be imputed using multiple imputations under the “missing at random” assumption and the results will be pooled. To control the global type I error rate with 5%, the Bonferroni Holm procedure will be applied. In case that at least one of the two comparisons can be considered significant, arm 1 vs. 2 will be compared at a significance level of 5%, still controlling the global significance level of 5%.

In addition, a complete case analysis will be carried out. In the per protocol set only patients who were treated as described in the protocol with complete documentation of relevant data will be considered. This set will be analyzed as well as sensitivity analysis.

Time to event endpoints will be analyzed using Cox proportional hazard models adjusting for the stratification variables used in the randomization procedure. All secondary endpoints will be descriptively analyzed using statistical methods as appropriate for the underlying distribution of the data.

Safety endpoints will be analyzed based on the safety population which comprises all patients who had at least 1 day of treatment, considered in the arm as treated. Rates of acute and chronic toxicity will be calculated together with corresponding 95 confidence intervals for group comparisons. Descriptive *p*-values for the chi-squared test will be provided. Statistical methods will be used to assess the quality of the data, homogeneity of treatment groups, endpoints and safety of the two intervention groups. Details of the statistical analysis will be fixed at the latest in the Statistical Analysis Plan (SAP) to be prepared before database closure. This also includes the definition of the analysis populations.

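### Non-inferiority of hypofractionation is announced as the secondary aim, but the planned analysis of those endpoints is descriptive and the trial was not sized for them

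*Protocol article*

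**What the plan says.** The Methods/ design paragraph of the abstract gives the aim: "Secondary aims are non-inferiority of hRT compared to nRT with regard to biochemical progression-free survival (bPFS), overall survival (OS), quality of life and toxicity".

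The body of the article does not return to it. The section on primary and secondary endpoints lists the same outcomes with time points and no hypothesis: "Secondary endpoints are bPFS after 5 years, quality of life (QoL) according to EORTC QLQ-C30 and –PR25 after 2 and 5 years", followed by toxicity at 2 and 5 years and OS at 5 years.

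The Statistical analysis section then fixes how they are handled:

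- In general: "All secondary endpoints will be descriptively analyzed using statistical methods as appropriate for the underlying distribution of the data".
- bPFS and OS: "Time to event endpoints will be analyzed using Cox proportional hazard models adjusting for the stratification variables used in the randomization procedure".
- Toxicity: "Rates of acute and chronic toxicity will be calculated together with corresponding 95 confidence intervals for group comparisons", with chi-squared p-values that are themselves labelled descriptive.

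The same section holds one inferential comparison of nRT with hypofractionated photons. If at least one of the two proton comparisons is significant, "arm 1 vs. 2 will be compared at a significance level of 5" per cent. It belongs to the procedure for the primary endpoint, the change in bowel score at 12 weeks. The Sample size calculation section rests on that endpoint alone and expects the two photon arms to be equal: "we assume a change of 6.5 points in arm 2 as well".

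**The concern.** Non-inferiority is a conclusion drawn against a margin: an interval must exclude a loss that was declared unacceptable beforehand. An analysis that is descriptive throughout has no such rule. The abstract therefore announces a conclusion that the stated analysis does not deliver. A margin added in the SAP would not remove the conflict, because the article's own text already says how all secondary endpoints will be analysed.

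The Discussion expects the results to shape management and treatment recommendations. If the arms look similar, the abstract gives a ready label for that result, although nothing in the shown text says how much loss of biochemical control or survival would have been ruled out. The aim also leaves the comparison open. Arms 2 and 3 are both hRT, but arm 3 changes the modality as well as the fractionation.

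**Working it through.** **1. The plan's own sample size.** Inputs from the Sample size calculation section: difference 6.5 − 2.5 = 4 points, SD 15, two-sided 2.5% per comparison, power 80%.

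Normal approximation: n = 2 × (15/4)² × (2.241 + 0.842)² = 28.125 × 9.505 = 267.3, so 268 per arm. With the exact noncentral t, power is 0.7991 at 268 and 0.8007 at 269, so the stated 269 is reproduced. Dropout: 269/0.9 = 298.9, so 299. Total: 3 × 299 = 897. The figures are correct, and they concern superiority of protons on the bowel score only.

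**2. Aim and analysis side by side.**

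| Outcome in the aim | Stated analysis | Margin or decision rule shown |
|---|---|---|
| bPFS, OS | Adjusted Cox model, descriptive | None |
| Quality of life (2 and 5 years) | Descriptive | None |
| Toxicity | Rates, 95% intervals, descriptive p-values | None |

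**3. What the trial could exclude.** The article gives no control rate for bPFS or OS. The nearest figure is a 4-year bPFS of 75% in a cited cohort of 56 men. The following are therefore assumptions: 5-year bPFS of 70–85%, 5-year OS of 95%, a true hazard ratio of 1, 269 evaluable men per arm (after the plan's 10% loss), all followed for 5 years, and one-sided 2.5% for non-inferiority.

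For arm 2 versus arm 1:

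- events E = 538 × (1 − S), where S is the 5-year rate
- SE of the log hazard ratio = √(4/E)
- upper 95% limit = exp(1.960 × SE)
- smallest margin with 80% power = exp((1.960 + 0.842) × SE)

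| Endpoint, assumed S | E | SE | Upper 95% limit | 80%-power margin |
|---|---|---|---|---|
| bPFS 70% | 161 | 0.157 | 1.36 | 1.55 |
| bPFS 75% | 134 | 0.172 | 1.40 | 1.62 |
| bPFS 85% | 81 | 0.223 | 1.55 | 1.87 |
| OS 95% | 27 | 0.386 | 2.1 | 2.9 |

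On the absolute scale, under proportional hazards, the upper limits at the ends of the bPFS range correspond to 0.70^1.36 = 0.62 and 0.85^1.55 = 0.78. Even with identical arms, the interval would on average still include a loss of about 7 to 8 percentage points in 5-year bPFS.

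**4. What a non-significant difference would mean.** Take control bPFS of 75% and a true hazard ratio of 1.3. Arm 2 is then at 0.75^1.3 = 0.688, and events are 269 × 0.25 + 269 × 0.312 ≈ 151. SE = √(4/151) = 0.163, and log(1.3)/0.163 = 1.61. The chance of a non-significant two-sided 5% result is Φ(1.96 − 1.61) ≈ 0.64. Over control rates of 65% to 90% it is 0.52 to 0.82.

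No comparable figure can be given for quality of life at 2 and 5 years or for toxicity, because the article states no SD or rates for them.

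**The case against.** The best defence is that non-inferiority appears only in the abstract. Read alone, the Methods promise estimates and no confirmatory claim, and a journal article may leave margins and analysis sets to the full protocol or SAP. This stands in part. The absence of a margin from the article is not itself the fault. What remains is that two statements in the same article conflict: one names a confirmatory aim, the other calls all of its endpoints descriptive.

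Three stronger readings are tempting, and the article does not support them.

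- A reader might infer that a non-inferiority claim could rest on nothing but a non-significant p-value. That goes too far. The Cox models give hazard ratios with intervals and the toxicity intervals are planned, so the raw material for a margin comparison exists. What is missing from the shown text is the rule, and without one any such conclusion would be post hoc.
- A reader might take the conditional comparison of arms 1 and 2 for the non-inferiority test and fault it because the plan expects those arms to be equal. The article never presents it that way. It concerns the week-12 bowel score, and rejecting 5% of the time when its null holds is what any valid test does. Taking the remaining pairwise equality at the full 5% after one rejection is sound.
- A reader might want to turn that comparison into a non-inferiority test with the plan's 4-point difference as margin. Those 4 points are the assumed proton benefit. Nothing in the article justifies them as a tolerable loss.

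**Conclusion.** The point holds as a contradiction between the abstract and the Statistical analysis section. As written, the trial cannot support a confirmatory non-inferiority conclusion for hRT on bPFS, OS, quality of life or toxicity. It can estimate these differences, with limited precision. With 269 per arm and truly equal arms, the upper 95% limit for arm 2 versus arm 1 is about 1.36–1.55 for bPFS and about 2.1 for OS. Margins with 80% power start at about 1.55–1.87 and 2.9.

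These sizes rest on assumed 5-year rates (bPFS 70–85%, OS 95%) and on complete 5-year follow-up of the evaluable men. The contradiction does not depend on them. Whether margins of that size would be acceptable is a clinical judgement on which the article is silent.

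This is a correction to a secondary aim. It would be wrong to infer that the proton comparisons or the trial size are compromised: 269, 299 and 897 are right for the primary endpoint.

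**What to change.** Bring the abstract's aim and the Statistical analysis section into line before outcome data are examined:

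- Reword the secondary aim as estimation of hypofractionated against normofractionated photon therapy, arm 2 versus arm 1, for bPFS, OS, quality of life and toxicity. This isolates fractionation. Arm 3 against arm 1 should be reported separately because it also changes modality.
- Report hazard ratios, mean differences or rate differences with 95% confidence intervals.
- State that no non-inferiority conclusion will be drawn for these endpoints. State also that a non-significant difference, including the conditional bowel-score comparison of arms 1 and 2, will not be read as non-inferiority.

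The cost is wording in the protocol and SAP, with no extra patients and no change to the primary analysis. The sponsor gives up a non-inferiority claim for these endpoints. If the full protocol or SAP already holds margins, the alternative is to correct the statement that all secondary endpoints are descriptive and to report the achievable power for each. On the figures above, that power would be low for narrow margins: a bPFS margin of 1.3 needs 457 events in arms 1 and 2, against about 81 to 161 expected.

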**Discussion:**

The present study aims to evaluate the role of hypofractionated radiotherapy to the prostate bed with photons and protons leading to significant impact on future management of operated men with prostate cancer.

**Trial registration:**

Deutsches Register klinischer Studien: DRKS00015231; registered 27 September 2018.

## Background

For patients with non-metastatic prostate carcinoma, surgery or radiotherapy with or without hormonal therapy (HT) are curative treatment options. After prostatectomy, irradiation can be performed as adjuvant therapy or after prostate specific antigen (PSA) rise. While several larger studies reported on the oncological benefit for postoperative radiotherapy [1, 2], there is only one prospective phase III trial evaluating the role of dose-escalated salvage irradiation so far [3]. One multicenter, prospective phase II study from Germany is currently analyzing the role of moderately dose-escalated salvage radiotherapy in combination with local hyperthermia [4].

For some years now, hypofractionated irradiation becomes more and more common for patients with prostate cancer. Many trials observed excellent clinical outcome after moderate hypofractionation for patients undergoing definitive radiotherapy [5–8]. As one of the largest studies, the CHHiP trial evaluated 3216 men with localized prostate cancer. With a median follow-up of 62.4 months, hypofractionated radiotherapy (hRT) with 60 Gy in 20 fractions was not inferior compared to conventional fractionation. At 5 years, 90.6% in the 60 Gy group and 88.3% in the 74 Gy group were free of biochemical or clinical failure [5]. Nowadays, hypofractionation is frequently proclaimed as the “new standard of care” for definitive radiotherapy of patients with prostate cancer. However, in the postoperative setting reliable data is missing with regard to hypofractionation. Few studies with mostly small numbers of patients reported on feasibility and toxicity. When using moderate hRT, postoperative radiotherapy seems to be safe and provided promising clinical results [9–11]. Lewis et al. observed no acute grade 3 toxicity and a 4-year bPFS of 75% in a cohort of 56 men. All patients obtained image-guided intensity-modulated radiation therapy (IMRT) in 2.5 Gy fractions [12]. Our institution also tested different approaches for hypofractionation after surgery: The PRIAMOS 1 trial evaluated treatment safety and toxicity of hRT of the prostate bed using IMRT and daily image-guidance. In this prospective phase II trial, 40 men received adjuvant or salvage irradiation with single doses of 3.0 Gy up to a total dose of 54.0 Gy. Treatment was tolerated well with no recorded side effects grade 3+ [13]. Very similar results were obtained when using proton therapy instead of photons. With the use of protons, patient-reported bowel-score according to EORTC QLQ-PR25 questionnaire was already improved at week 10 and reached borderline significance when compared to photon therapy [*data unpublished*]. Therefore, larger and randomized trials are of great interest evaluating the role of hRT for patients after prostatectomy.

The PAROS trial is designed as a prospective, multicenter and randomized 3-arm phase III trial evaluating toxicity and efficacy of hypofractionation for prostate cancer patients undergoing adjuvant or salvage irradiation.

## Methods

### Primary and secondary endpoints

The primary endpoint is defined as the change in the bowel-score according to EORTC QLQ-PR25 from baseline to 12 weeks after start of proton therapy compared to photon irradiation.

Secondary endpoints are bPFS after 5 years, quality of life (QoL) according to EORTC QLQ-C30 and –PR25 after 2 and 5 years, clinical symptoms and toxicity according to National Cancer Institute Common Terminology Criteria for Adverse Effects (NCI CTCAE) version 5.0 after 2 and 5 years as well as overall survival (OS) after 5 years.

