### Follow-up/ evaluation of efficacy and safety parameters

The first follow-up examination will be performed at 12 weeks after the start of irradiation. While regular urooncological aftercare will be organized according to national guidelines, follow-up vists within the trial will be scheduled after 6, 12, 24, 36 and 60 months (Table 1). PSA levels can also be received from the treating urologist every 3months for the first 2 years and semi-annually thereafter.

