**Table 1 Tab1:**
[figure not shown]
Time schedule for the present trial

*RT* radiotherapy, *PSA* prostate specific antigen, *CT* computed tomography, *QoL* quality of life

*obtained from treating urologist or participating radio oncological center

grey = postal query or query by phone is permitted

Acute and chronic toxicity will be evaluated according to NCI CTCAE version 5.0 during and after the treatment. EORTC QLQ-C30 and -PR25 questionnaires are used to collect data on QoL.

Biochemical failure is defined as two consecutive increases of PSA from nadir according to national guidelines [14–17]. bPFS is defined as time from first diagnosis to biochemical failure. OS is defined as time from the first diagnosis to death from any course. If the respective event has been observed, the patient is censored at the date of the last follow-up examination.

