## Discussion

After prostatectomy, irradiation is recommended for several patients with prostate cancer due to various criteria like positive resection margins or PSA relapse. Although prostate specific membrane antigen (PSMA) positron emission tomography (PET)/CT is now available for recurrent disease, detection rates are limited; especially for low and very low PSA levels. Several studies reported on a probability of about 50% in detecting macroscopic tumor at PSA levels of < 0.5 ng/ml [18, 19]. Currently, there is no evidence for prolonging adjuvant or salvage radiotherapy to reach higher detection rates from PSMA PET/CT. Therefore, radiotherapy is often prescribed to the prostate bed assuming this localization has the highest risk for prostate cancer cells.

Today, nRT with photons is considered as the standard of care for patients undergoing irradiation after prostatectomy. However, treatment time covers a period of several weeks for each patient so far. Due to the low α/β value of prostate cancer compared to relevant normal tissue, hypofractionation seems to be feasible and safe without an increase of late reactions. However, inconsistent data exist so far with regard to chronic side effects: While several studies reported on similar late toxicity when using postoperative, hRT [12, 20], Cozzarini et al. observed a higher risk of late urinary toxicity in a relatively small group of patients who underwent hypofractionation. In this retrospective analysis, the 5-year risk of severe (grade ≥ 3) late urinary side effects increased in the heterogeneous cohort of patients treated with different hRT regimes compared to men treated with normofractionation [21]. Even though results should be interpreted with caution due to the retrospective character of the study and the small number of patients in the different hRT subgroups, additional research is imperative.

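### Late toxicity over 5 years is to be compared as crude rates with a chi-squared test, which makes no allowance for death, loss to follow-up or, on one reading, resolved events

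*Protocol article*

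**What the plan says.** Under Primary and secondary endpoints, the protocol article sets toxicity by CTCAE "version 5.0 after 2 and 5 years as well as overall survival (OS) after 5 years". The same sentence also attaches a 5-year time point to biochemical progression-free survival.

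The Follow-up section has a first examination at 12 weeks and further visits "scheduled after 6, 12, 24, 36 and 60 months". The text below Table 1 adds: "Acute and chronic toxicity will be evaluated according to NCI CTCAE version 5.0 during and after the treatment".

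Under Statistical analysis, the set, the measure and the test are named:
- Set: "Safety endpoints will be analyzed based on the safety population which comprises all patients who had at least 1 day of treatment", taken in the arm as treated.
- Measure: "Rates of acute and chronic toxicity will be calculated together with corresponding 95 confidence intervals for group comparisons".
- Test: descriptive p-values "for the chi-squared test will be provided".

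Cox models are planned for time-to-event endpoints. Only biochemical progression-free survival and overall survival are defined as times to an event. Multiple imputation is planned for the primary endpoint only. Further details are left to the SAP.

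**The concern.** The Abstract lists toxicity among the aims on which hypofractionation is to be shown non-inferior to normofractionation. The Discussion gives the reason for caution: in a retrospective cohort treated with hypofractionation, "the 5-year risk of severe (grade ≥ 3) late urinary side effects increased". A 5-year risk is a cumulative quantity over follow-up. A crude proportion with a chi-squared test treats follow-up as complete and equal for all patients. Over 60 months it will not be, since the plan itself expects drop-out and has overall survival as an endpoint.

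An under-count that is similar in all arms shrinks the absolute difference between them. For an aim of showing that hypofractionation is no worse, that error runs in the favourable direction. It would also make the result hard to set against the 5-year risk that motivated the question.

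**Working it through.** **The plan's own figures.** There is no expected rate, margin or power for late toxicity to reproduce. The only loss figure is 10%, in the Sample size calculation for the 12-week primary endpoint: 269 / 0.9 = 298.9, so 299 per arm and 3 × 299 = 897. That reproduces, but it says nothing about loss at 5 years.

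**Assumed inputs.** True 5-year risk 10% (5% in a comparison arm); 10% to 30% of patients not followed to 5 years; late events starting evenly between months 3 and 60, with exponential duration of mean 6 to 48 months. None of these is in the document.

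The text allows three readings of a late-toxicity rate.

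**Reading 1: status at the visit.** Simulated share of late events present at the visits:

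| Mean duration (months) | Month 60 only | Month 24 or 60 | Any of 6, 12, 24, 36, 60 |
|---|---|---|---|
| 6 | 10.5% | 20.7% | 39.3% |
| 12 | 20.9% | 37.4% | 57.7% |
| 24 | 38.3% | 57.3% | 74.1% |
| 48 | 58.6% | 74.3% | 85.4% |

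The first column agrees with the closed form (d/57) × (1 − exp(−57/d)); for d = 24 this is 0.421 × 0.907 = 0.382. With mean durations of 12 to 48 months, a true cumulative risk of 10% would read 10% × 0.209 = 2.1% to 10% × 0.586 = 5.9% at month 60, before any loss. Counting unassessed patients as event-free multiplies this by a further (1 − u), where u is the share unobserved.

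**Reading 2: worst grade to date, all treated patients in the denominator.** Recorded events are kept. With a constant hazard, 5λ = −ln(0.9) = 0.1054. A patient who leaves at a time uniform over 5 years has an average recorded risk of 1 − 0.1/0.1054 = 5.1%. The crude rate is (1 − u) × 10% + u × 5.1%:
- u = 10%: 9.5%
- u = 20%: 9.0%
- u = 30%: 8.5%

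For a true 5% the same formula gives 4.75% and 4.5% at u = 10% and 20%. A true 5-point excess then reads 9.5 − 4.75 = about 4.8 points, or 9.0 − 4.5 = 4.5 points. Under this reading the shortfall comes from loss. A patient who dies without toxicity stays in the denominator without an event, as in a competing-risk estimate.

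**Reading 3: only patients observed at 5 years in the denominator.** If a is the share of patients with an event who are not observed and u the share of all patients not observed, the rate is 10% × (1 − a)/(1 − u). It stays at 10% if a = u, falls if a > u and rises if a < u. Patients who died, and the partial follow-up of all who left, are dropped.

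Each reading therefore has a defect, and the defects differ in size and direction.

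**The case against.** The strongest case against is that the document fixes neither reading 1 nor the treatment of unassessed patients. The sentence that sets toxicity at 2 and 5 years uses the same form for overall and biochemical progression-free survival, which are not visit-day states. Rates of acute toxicity are also planned, and these cannot come from 2- and 5-year readings. So worst grade to date fits the text. Naming the safety population does not say that a patient without a 5-year assessment counts as free of toxicity. The p-values are descriptive, the article sets no toxicity margin, and details go to a SAP that is not shown.

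Most of this stands. A reader might infer that late toxicity is certain to be understated, and by about half. For example, with true risks of 10% and 5%, 30% to 50% of events resolved and 10% to 20% of patients unobserved, the rates are 10% × 0.7 × 0.9 = 6.3% against 3.15%, or 10% × 0.5 × 0.8 = 4.0% against 2.0%. A 5-point excess would then show as 3.15 to 2.0 points. The document does not support this as a conclusion. It needs status at the visit, missing counted as event-free and inputs found nowhere in the text. The risk ratio would remain 2.0 throughout.

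Deferral to the SAP does not remove the point. The article does more than stay silent: it names a crude rate and a chi-squared test, and keeps time-to-event methods for other endpoints. A SAP that only filled in details would keep that method.

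**Conclusion.** The concern holds as a weakness in the stated method. A crude proportion with a chi-squared test makes no allowance for death or loss over 5 years, and if the rates are visit-day status it also omits resolved events. It is a poor match to the cumulative 5-year risk raised in the Discussion and to the non-inferiority aim in the Abstract.

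A definite downward bias is not established. With worst grade to date over all treated patients and 10% to 20% even loss, the error is modest: a true 10% reads about 9.5% to 9.0%. With point prevalence it could be much larger, depending on how long events last. With an observed-only denominator its direction is open. All these sizes rest on assumed risks, durations and losses. As toxicity is a secondary endpoint with descriptive testing, this is an improvement worth making and does not threaten the primary result.

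**What to change.** In Statistical analysis, make the main late-toxicity summary the cumulative incidence, up to 2 and 5 years, of first grade 2 or higher and of first grade 3 or higher late toxicity, separately for genitourinary and gastrointestinal events. Use all CTCAE assessments, treat death as a competing event and censor at the last toxicity assessment. Report between-arm differences with 95% confidence intervals. Keep prevalence at 2 and 5 years as an additional description, with only patients assessed at that visit in the denominator. Word the endpoint under Primary and secondary endpoints to match.

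The cost is a change of wording before database closure and a little more analysis. Onset will be known only to within a visit interval, and censoring assumes that loss is unrelated to toxicity. The article says toxicity is evaluated during and after treatment, but the schedule in Table 1 is not visible here. The sponsor should therefore confirm that CTCAE grades are recorded at each visit and whether the form captures events since the previous one.
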